## Abstract

**Background/Objectives:** Quadriceps arthrogenic muscle inhibition (AMI) represents a key impairment following anterior cruciate ligament reconstruction (ACLR), contributing to quadriceps weakness. Although transcutaneous electrical nerve stimulation (TENS) and percutaneous electrical nerve stimulation (PENS) have been primarily investigated for analgesia, their effects on quadriceps strength in the early postoperative period remain underexplored. **Methods:** This study describes a single-blinded, parallel-group randomized controlled trial investigating the short-term effects of a single high-frequency TENS session and a novel long-term potentiation (LTP) PENS protocol on quadriceps strength and related clinical outcomes after ACLR. Fifty-four participants will be randomly allocated using block randomization in a 1:1:1 ratio to one of three groups: a control group (conventional post-ACLR rehabilitation only), a TENS group (conventional rehabilitation plus a single high-frequency TENS session), or a PENS group (conventional rehabilitation plus a single LTP PENS session). Participants will receive neuromodulatory intervention during the sixth postoperative week. The LTP PENS protocol consists of five 5 s stimulation bursts at 100 Hz and 250 μs pulse width and has only been investigated once in patients with upper limb pathology, underscoring its novelty in a postoperative setting. **Results:** The primary outcome is quadriceps maximal voluntary isometric contraction, selected as a clinically relevant surrogate of quadriceps activation deficits associated with AMI. Secondary outcomes include pain intensity, pressure pain threshold, knee range of motion, thigh muscle perimeter, knee effusion and swelling, and self-reported function and knee-related quality of life. Outcomes will be assessed at baseline, immediately post-treatment, and 1 and 7 days post-intervention by a blinded assessor.

## 1. Introduction

The anterior cruciate ligament (ACL) plays a critical role in knee stability, serving as the primary restraint against anterior tibial translation throughout the full range of knee flexion. ACL deficiency increases anterior subluxation of the tibiofemoral compartments under combined loads of anterior translation, internal rotation, and valgus stress, as observed in the pivot-shift phenomenon [1,2,3]. Moreover, the ACL contributes to controlling internal rotation, particularly near full extension [1,2,4].

ACL injuries are prevalent in the general population. Recent epidemiological data indicate that the annual incidence of ACL rupture is approximately 75 per 100,000 person-years in the general population of the United States, with higher rates observed among females (51.2%) and adolescents aged 10–19 years [5,6].

The American Academy of Orthopedic Surgeons recommends ACL reconstruction (ACLR) for patients with persistent instability, particularly young and physically active individuals, to restore knee stability, optimize joint function, and prevent secondary meniscal and cartilage damage [7]. Commonly used grafts include hamstring tendon autografts, bone–patellar tendon–bone autograft, quadriceps tendon autograft, and allografts. Autografts are generally favored in younger, active patients, whereas allografts are typically reserved for older or lower-demand populations [8,9,10].

Importantly, concomitant procedures to improve knee stability are increasingly performed. Since the description of the anterolateral ligament (ALL) in 2012, lateral extra-articular tenodesis (LET) has regained attention as an adjunct to ACLR to improve rotational stability [11,12,13,14,15]. Commonly applied techniques include the modified Lemaire and Arnold–Cocker procedures [13,16,17]. In the context of early quadriceps recovery, these procedures may influence neuromuscular activation patterns and postoperative rehabilitation; therefore, their potential impact is acknowledged in this trial.

Despite advances in surgical techniques and postoperative management, ACL re-rupture rates remain clinically relevant. Reported rates vary according to age, graft type, surgical technique, and activity level, ranging from 3.9% to 9% in the general population over 3–5 years, and reaching up to 19.7% among high-level athletes undergoing hamstring tendon reconstruction [18,19,20].

Following ACLR, the graft undergoes osseointegration at the tunnel interface and intra-articular remodeling, commonly referred to as ligamentization [21,22]. Understanding the biological processes and timing of each phase of graft healing is essential to optimize rehabilitation protocols and identify activities that may place excessive strain on the graft [21,23].

Quadriceps arthrogenic muscle inhibition (AMI) is a key impairment following anterior cruciate ligament reconstruction (ACLR), leading to persistent quadriceps weakness, altered neuromuscular activation, motor control deficits, and biomechanical gait alterations [24,25,26]. AMI arises from both peripheral and central mechanisms. Peripherally, inflammation, pain, and joint effusion alter afferent input from joint mechanoreceptors, resulting in reflex inhibition of quadriceps alpha motor neurons. Centrally, decreased corticospinal excitability and cortical plasticity changes reduce neural drive to the quadriceps, perpetuating impaired muscle activation [27,28].

These alterations lead to changes in muscle activation patterns and reduced motor unit recruitment, resulting in decreased quadriceps maximal voluntary contraction. Consequently, effective management of AMI during rehabilitation is essential to optimize early quadriceps activation [24,25,27]. The underlying peripheral and central mechanisms provide a rationale for targeted neuromodulatory interventions that may facilitate the restoration of quadriceps activation and strength.

Transcutaneous and percutaneous electrical nerve stimulation (TENS and PENS, respectively) have been predominantly investigated for analgesic effects [29,30,31,32]. However, evidence regarding their effectiveness on muscle strength remains limited. As far as we are aware, clinical trials investigating primarily pain outcomes with PENS are more numerous [33,34,35,36,37,38,39,40] than those focusing on quadriceps-specific strength outcomes [41], with only one study including a postoperative patient [40].

Although AMI is fundamentally a neural activation deficit, quadriceps maximal voluntary isometric contraction (QMVIC) was selected as the primary outcome because it represents a clinically relevant surrogate of the functional consequences of impaired quadriceps activation [42,43]. Accordingly, this study adopts a clinical-functional perspective, hypothesizing that TENS and PENS exert their effects primarily through direct neuromodulatory influences on muscle activation rather than solely via pain reduction.

A single-session intervention was deliberately chosen to assess the ability of neuromodulatory techniques to acutely enhance quadriceps activation during a critical postoperative period characterized by persistent AMI. The sixth postoperative week represents a clinically relevant time point: biological graft healing following the early healing phase permits safe neuromuscular loading, while neuromuscular inhibition persists despite conventional post-ACLR rehabilitation program (CRP) [21]. High-frequency TENS and a long-term potentiation (LTP) PENS protocol were selected for their capacity to induce rapid changes in neural excitability [44], enabling evaluation of whether even a single session can produce clinically meaningful improvements when combined with CRP. Moreover, to our knowledge, the administered LTP PENS protocol has previously been investigated only once in patients with arm pathology, underscoring its novelty in a postoperative context [45].

Accordingly, the primary objective of this randomized controlled trial is to determine whether adding a single session of high-frequency TENS or the novel LTP PENS protocol to a conventional post-ACLR rehabilitation program improves quadriceps maximal voluntary isometric contraction compared with rehabilitation alone.

Secondary objectives include evaluating the effects of these interventions on key clinical outcomes, including pain intensity, pressure pain threshold, knee range of motion, thigh muscle perimeter, intra-articular knee effusion, extra-articular knee swelling, and self-reported function and knee-related quality of life.

Exploratory analyses will assess whether these effects vary according to graft type or concomitant surgical procedures, contributing to a more precise understanding of how neuromodulatory rehabilitation strategies can be tailored to specific surgical approaches and patient characteristics. Aligning rehabilitation with surgical technique may inform more individualized, efficient, and evidence-based postoperative management.

## 2. Materials and Methods

The current study protocol follows the Standard Protocol Items: Recommendations for International Trials (SPIRIT) [46].

### 2.1. Study Design and Setting

A single-blinded randomized controlled trial will be conducted at Clínica CEMTRO (FIFA Medical Centre of Excellence), Madrid, Spain, in accordance with Consolidated Standards of Reporting Trials (CONSORT) guidelines [47,48]. The intervention and follow-up period for participants will be 7 days.

### 2.2. Ethics Approval and Enrollment of Participants

The study will be conducted in accordance with the Declaration of Helsinki [49,50] and the Spanish Law on Personal Data Protection and Guarantee of Digital Rights [51]. The protocol was approved by the Medical Direction for Education and Research and the Directorate of the Physiotherapy Department of Clínica CEMTRO, and subsequently by the Institutional Review Board (or Ethics Committee) of Universidad Católica San Antonio de Murcia (Protocol Code: CE112417). The trial was registered in the ClinicalTrials.gov database (identifier NCT06910150).

Patients beginning postoperative rehabilitation after anterior cruciate ligament reconstruction (ACLR) at Clínica CEMTRO will be invited to participate. Those who agree will sign an initial informed consent form authorizing the principal investigator to access their medical records and contact them directly. During the initial clinical assessment, participants will receive detailed information about the study and have the opportunity to ask questions. Volunteers meeting the inclusion criteria will then provide a second informed consent form and will receive a withdrawal form, with verbal reminders that they may revoke consent at any time without justification. Participants’ autonomy and data confidentiality will be ensured throughout the study.

### 2.3. Sample Size Calculation

Sample size was calculated using G*Power software (version 3.1) [52] for a repeated-measures analysis of variance with three groups. Assuming a medium effect size (f = 0.25), a power of 80% (β = 0.20), and a two-sided significance level of α = 0.05, a total sample size of 45 participants was required. The calculation was based on a correlation among repeated measures of 0.5 and a nonsphericity correction factor (ε) of 1. To account for an anticipated dropout rate of 20%, a total of 54 participants will be recruited, with 18 allocated to each group (control, TENS, and PENS).

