### 2.5. Allocation and Randomization

The randomization sequence will be generated by an independent statistician not involved in participant recruitment or outcome assessment. Randomization will be conducted prior to study initiation using Research Randomizer v4.0 [58]. Block randomization with a block size of three will ensure an equal number of participants across the three study groups [59]. A total of 54 participants will be allocated in 18 blocks of three, with each block containing one assignment to each group (1 = control, 2 = TENS, 3 = PENS), without repetition or predetermined order.

Stratified randomization by graft type or concomitant procedures was not implemented; participants were randomized without stratification to maintain study feasibility and integrity.

To ensure allocation concealment, the generated randomization sequence will be implemented using individual, sequentially numbered index cards indicating the assigned group. The cards will be placed in sealed opaque envelopes, which will be opened only after baseline assessments are completed by an independent assessor. This approach prevents recruitment and enrollment personnel from predicting future allocations, even with block randomization of size three. By combining independent sequence generation with secure envelope implementation, selection bias is minimized while ensuring correct assignment of the intervention.

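### 54 recruits do not cover 20% dropout from a requirement of 45: about 43 completers remain, and 54 allows for only 16.7%

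*Protocol article*

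**What the plan says.** Section 2.3 (Sample Size Calculation) describes a G*Power calculation "for a repeated-measures analysis of variance with three groups" and concludes that "a total sample size of 45 participants was required". It then adds the allowance for losses: "To account for an anticipated dropout rate of 20%, a total of 54 participants will be recruited, with 18 allocated to each group". Section 2.5 (Allocation and Randomization) builds the same total into the allocation list: "A total of 54 participants will be allocated in 18 blocks of three". The abstract also gives 54. No other part of the article states a different dropout rate or a larger recruitment target.

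The order of the text matters. The 45 is presented as the number needed, and dropout is dealt with afterwards. The 54 is therefore offered as the recruitment figure that still delivers 45 after a 20% loss.

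**The concern.** A dropout rate is a proportion of the people who enter the trial. Recruitment must therefore be the required number divided by one minus the rate. Adding 20% of the required number gives a smaller total, and the final count falls short of the requirement.

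The shortfall bears on the analyses that need complete data. Section 2.9 (Statistical Methods) plans a repeated-measures ANOVA, the type of analysis used to size the trial, and a per-protocol analysis limited to participants who attend every scheduled assessment. Section 2.4 also lists absence from measurement sessions and voluntary withdrawal among the exclusion criteria, so a missed visit may remove a participant altogether. The dropout allowance is the only stated protection for these analyses, and it is smaller than claimed.

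**Working it through.** **Inputs**
- Required total: 45 (section 2.3).
- Anticipated dropout: 20% (section 2.3).
- Recruited total: 54, 18 per group (section 2.3), in 18 blocks of three (section 2.5).
- Effect size f = 0.25, correlation ρ = 0.5, ε = 1, α = 0.05, k = 3 groups (section 2.3).
- Number of measurements m: not given in section 2.3. The assessment schedule in section 2.8 has four.

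**Step 1. Reproduce the plan's figure.** 45 × (1 + 0.20) = 54.0, an exact match. The article does not show this step, so the cause is inferred from the match.

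**Step 2. Apply the stated dropout to the stated recruitment.** 54 × (1 − 0.20) = 43.2 in total, or 18 × 0.80 = 14.4 per group. The requirement is 45, or 15 per group.

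**Step 3. Find the dropout that 54 does cover.** 1 − 45/54 = 9/54 = 16.7%.

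**Step 4. Find the recruitment that covers 20%.** 45/(1 − 0.20) = 56.25. Rounding up gives 57, which is also a multiple of three (19 per group, 19 blocks). Check: 57 × 0.80 = 45.6.

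**Step 5. Chance of keeping at least 45.** Assume that each patient drops out independently with probability 0.20.
- 54 recruited: P(Bin(54, 0.8) ≥ 45) = 0.34.
- 57 recruited: P(Bin(57, 0.8) ≥ 45) = 0.65.

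**Step 6. Cost in power.** Section 2.3 does not say which effect was powered, so both effects that compare groups are shown, with G*Power's default definition of effect size and the noncentral F distribution.
- Group × time interaction: λ = N·m·f²/(1 − ρ), with (k − 1)(m − 1) and (N − k)(m − 1) degrees of freedom. For N = 45 and m = 4, λ = 45 × 4 × 0.0625/0.5 = 22.5.
- Between groups: λ = N·m·f²/(1 + (m − 1)ρ), with k − 1 and N − k degrees of freedom. For N = 45 and m = 4, λ = 45 × 4 × 0.0625/2.5 = 4.5.

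| Effect | m | Power at 45 | Power at 43 |
|---|---|---|---|
| Interaction | 2 | 0.8336 | 0.8140 |
| Interaction | 3 | 0.9109 | 0.8955 |
| Interaction | 4 | 0.9555 | 0.9451 |
| Between groups | 2 | 0.3682 | 0.3524 |
| Between groups | 3 | 0.4088 | 0.3914 |
| Between groups | 4 | 0.4327 | 0.4144 |

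The loss from 45 to 43 is between 1.0 and 2.0 percentage points in every row.

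**The case against.** The arithmetic is not in dispute. The case on the other side is about weight, and much of it stands.

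- **The correction changes no power conclusion.** For the interaction, 43 completers still exceed 80% power at two, three or four measurements. For the between-group effect, both 45 and 43 fall far short. Three more recruits do not move either case across the target.
- **The 45 is itself uncertain.** It does not reproduce from the stated inputs at 80% power. With four measurements the interaction needs 30 and the between-group effect about 102. That is a separate and larger weakness of the same section. The interaction with three measurements needs 36, and 36/0.80 = 45, so 45 might already include dropout. That is speculation, and it conflicts with the text, which states 45 as required and adds dropout afterwards.
- **The primary analysis does not need complete cases.** Section 2.9 names an intention-to-treat linear mixed model that uses all available data. Baseline, intervention and the immediate post-treatment assessment follow one another closely, so a patient lost before 24 hours or 7 days would usually still contribute. The figure of 43 is the expected number of full completers, not the number in the primary analysis.
- **The 34% needs its comparator.** Even 57 gives only about 65%, because sizing on the expected number of completers never guarantees the target.

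None of this makes the sentence true. It claims that 54 absorbs a 20% loss from a requirement of 45, and it does not. This is a false statement and not a detail left to a fuller document, so no analysis plan could repair it.

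**Conclusion.** The concern holds. With 20% dropout, 54 recruits yield an expected 43.2 completers, about two fewer than the plan's own requirement. The recruited number covers 16.7% dropout, not 20%. The trial is more likely than not to miss 45 completers (chance of reaching it about 34%, assuming independent dropout at 20%).

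The consequence is modest: one to two points of power for the effects that compare groups, under the default effect-size definition, and less harm to the primary mixed model than to the ANOVA and per-protocol analyses. The conclusion takes 45 at face value as the number needed after losses, as section 2.3 presents it. It should be corrected because this sentence is the stated justification for the trial's size and any reader can check it.

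**What to change.** Correct the sentence in section 2.3 in one of three ways.

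1. **Keep 54 and restate the allowance:** *54 randomised participants allow for up to 16.7% dropout while retaining 45 completers.* This costs one sentence and no extra enrolment.
2. **Keep 54 and 20%, and restate the yield:** *With 20% dropout, 54 randomised participants give about 43 completers*, followed by the power at 43. This also requires section 2.3 to name the effect tested and the number of measurements, because the power at 43 cannot be stated without them.
3. **If 20% must be covered, recruit 57 (19 per group).** This means three more patients, an allocation list of 19 blocks of three in section 2.5, and the new total wherever 54 appears, including the abstract.

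Options 1 and 2 make the stated figure slightly less favourable but leave the conduct of the trial unchanged. Either is sufficient.

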### 2.4. Participants and Eligibility Criteria

Eligible patients will be aged 18–55 years old and will have undergone ACLR within the previous six weeks using hamstring tendon (HT), patellar tendon (BPTB), quadriceps tendon autografts, or allografts at Clínica CEMTRO. ACLR may be accompanied by concomitant surgical procedures on one or both menisci (repair, debridement, rasping, partial meniscectomy) and/or a Lemaire lateral extra-articular tenodesis. All patients will provide written informed consent.

Exclusion criteria will include: (1) contraindications for invasive procedures [53]; (2) contraindications for dynamometric assessment [41]; (3) history of lumbar hernia or protrusion; (4) receipt of alternative treatments outside the study (e.g., analgesics); (5) neuropathic pain in the lower limbs; (6) central nervous system disorders [39]; (7) history of neurological disorders or spinal surgery; (8) inability to reliably complete self-reported questionnaires [54]; (9) Personal Psychological Apprehension Scale score > 37.5 [55]; (10) absence from scheduled measurement sessions; and (11) voluntary withdrawal from the study.

The Personal Psychological Apprehension Scale (PPAS) is a valid and reliable instrument that provides a useful tool for assessing participants’ subjective perceptions. The PPAS consists of 15 items, each with four response options: (1) very rarely, almost never; (2) occasionally, hardly ever; (3) frequently, quite often; and (4) continuously, almost always. Total scores range from a minimum of 15 points to a maximum of 60 points [55].

This criterion is applied to ensure participant safety and compliance, because individuals with high psychological apprehension may experience discomfort or adverse reactions during the intervention. Notably, the same PPAS-based exclusion criterion has been applied in previous studies involving invasive physiotherapy interventions [56,57].

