### 2.8. Outcomes

Assessments will be conducted at four time points: pre-treatment (A1), immediately post-treatment (A2), 24 h post-treatment (A3), and 7 days post-treatment (A4). All assessments will be conducted by an assessor blinded to group allocation and will be performed in the same clinical setting at Clínica CEMTRO (Madrid, Spain), under standardized conditions. The order of outcome assessment will be identical whenever applicable. All outcomes will be assessed according to the schedule presented in Table 2.

Baseline descriptive variables will include sex, age, body mass, height, BMI, limb dominance, operated limb, graft type (hamstring tendon autografts, bone–patellar tendon–bone autografts, quadriceps tendon autografts or allografts), associated lateral extra-articular tenodesis, and meniscal procedures (none, repair, debridement, rasping, partial meniscectomy). Surgery-related sensory disturbances (none, anesthesia, hypoesthesia, hyperesthesia, paresthesia) will also be recorded.

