### 2.9. Statistical Methods

All statistical analyses will be performed using SPSS statistical software for Windows (version 27.0; SPSS Inc., Chicago, IL, USA). The primary analysis will be conducted according to an intention-to-treat approach, using linear mixed-effects models, which accommodate repeated measures and handle missing data under the missing-at-random assumption.

A complementary per-protocol analysis will be conducted as a sensitivity analysis, including only participants who complete the assigned intervention and all scheduled assessments according to predefined criteria. This dual approach allows evaluation of the robustness of the primary findings.

Data normality will be assessed using the Shapiro–Wilk test. Descriptive statistics will be calculated for baseline characteristics, reporting means and standard deviations for normally distributed variables, and medians with interquartile ranges for non-normally distributed variables.

To evaluate intervention effects over time, repeated-measures analysis of variance (ANOVA) will be applied to outcomes meeting normality assumptions. The within-subject factor will be time (pre-treatment, immediate post-treatment, 24 h post-treatment, and 7 days post-treatment), and the between-subject factor will be group (control: CRP only; TENS: CRP plus a high-frequency TENS session; PENS: CRP plus a LTP PENS session). Bonferroni correction will be used for post hoc comparisons. Sphericity assumptions will be assessed, and Greenhouse–Geisser corrections will be applied as appropriate.

To provide a more flexible and robust analysis of repeated measures, linear mixed-effects models will additionally be applied. These models will include the fixed effects of group, time, and the group × time interaction. They allow inclusion of all available data and appropriately handle missing observations under the missing-at-random assumption without requiring complete cases or sphericity.

Exploratory multivariable analyses will be performed to investigate associations between clinical outcomes and sociodemographic and surgical-related variables, focusing on relationships with surgical procedures. Potential confounding effects of graft type and concomitant procedures on early quadriceps outcomes will not be formally tested, and any subgroup analyses will be limited to descriptive reporting.

A two-sided significance level of α = 0.05 will be adopted, and results will be reported with 95% confidence intervals.

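### Exclusion criteria (10) and (11) are not limited to the time before allocation, so as written they conflict with the intention-to-treat primary analysis

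*Protocol article*

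**What the plan says.** Section 2.4 gives one list of eleven exclusion criteria. The last two are "10) absence from scheduled measurement sessions; and (11) voluntary withdrawal from the study". The list also contains "4) receipt of alternative treatments outside the study (e.g., analgesics" with no period attached. Nothing in the section says that any of these criteria stops applying once a patient has been allocated.

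Section 2.5 places allocation after baseline: it says of the sealed envelopes "which will be opened only after baseline assessments are completed by an independent assessor". Section 2.8 gives the four sessions as "pre-treatment (A1), immediately post-treatment (A2), 24 h post-treatment (A3), and 7 days post-treatment (A4". Section 2.2 tells participants that "they may revoke consent at any time without justification", and Section 2.1 adds "The intervention and follow-up period for participants will be 7 days".

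Section 2.9 states: "The primary analysis will be conducted according to an intention-to-treat approach, using linear mixed-effects models". Of these models it says: "They allow inclusion of all available data and appropriately handle missing observations under the missing-at-random assumption without requiring complete cases or sphericity". The same section defines the per-protocol sensitivity set as patients who finish the assigned intervention and attend every scheduled assessment, subject to predefined criteria. It presents the pair of analyses as a check on robustness.

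**The concern.** Missing a follow-up visit and withdrawing are things that happen to a patient in the course of a trial. When they stand in an exclusion list, a trial team can read them as grounds for taking a randomised patient out. Section 2.9 gives the opposite instruction for the same patient.

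What is at stake is the population of the primary analysis. The outcome assessor is blinded, but participants and the treating clinician are not. The arms differ visibly: rehabilitation alone, rehabilitation plus surface current, or rehabilitation plus a needle. Attendance and withdrawal could therefore depend on arm and on early response, and exclusion on that basis would lose the protection of randomisation. The robustness check would also lose most of its content, because the primary set would come close to the per-protocol set. While both rules stand, the choice between them could be made after the data are seen.

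**Working it through.** **1. Timing of the events.** The order follows from Sections 2.5, 2.7 and 2.8: consent, A1, envelope opened, intervention, A2, A3 (24 h), A4 (7 days).

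- Criterion (10): a patient who misses A1 never reaches the envelope. Among randomised patients the criterion can therefore act only through A2, A3 or A4.
- Criterion (11): withdrawal is possible at any time. It can fall between consent and the opening of the envelope, or after it. Section 2.7 places the intervention immediately after A1, so most of the time at risk lies in the 7 days that follow.

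**2. The two rules side by side.**

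| Randomised patient | Section 2.4 as written | Section 2.9, primary analysis | Section 2.9, per-protocol |
|---|---|---|---|
| Attends A1–A4, completes intervention | in | in | in |
| Misses A3 only | excluded | in, with A1, A2, A4 | out |
| Withdraws after A2 | excluded | in, with A1, A2 | out |
| Attends A1–A4, departs from assigned intervention | in | in | out |

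Rows two and three are the conflict. Under Section 2.4 as written, the primary and per-protocol sets differ only through the last row and whatever the predefined criteria add.

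**3. Numbers affected.** Inputs from Section 2.3: 45 required, 20% dropout, 54 recruited, 18 per arm.

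- The plan's own step: 45 × 1.20 = 54, which reproduces the recruited figure.
- Affected at 20% dropout: 54 × 0.20 = 10.8, about 11.
- Remaining: 54 × 0.80 = 43.2, about 43, which is below 45. This shortfall comes from multiplying by 1.20; dividing gives 45 / 0.80 = 56.25, or 57. That is a separate point.

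**4. Power.** Inputs: noncentral F, f = 0.25, 3 groups, 4 measurements, correlation 0.5, ε = 1, α = 0.05. Moving from 54 to 43 patients changes power from 0.984 to 0.945 for the group × time interaction and from 0.511 to 0.414 for the between-group test. (The stated 45 is not reproduced by this formula in any variant tried; that too is separate and is not relied on here.) On the interaction test the loss of power is small, so the main concern is bias.

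**5. Bias, under an assumed mechanism.** Assume no true effect, equal variances (SD 1 at each visit) and correlation 0.5. The k poorest A2 responders of 18 in one arm drop out and no one is lost in the comparator.

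- Variance of the A1-to-A2 change: 2 × (1 − 0.5) = 1.
- Covariance of the A1-to-A2 and A1-to-A4 changes: 0.5 − 0.5 − 0.5 + 1 = 0.5. The regression slope is therefore 0.5.
- The expected lowest four of 18 standard normal values are −1.820, −1.350, −1.066 and −0.848, with sum −5.084.
- k = 1: completers' mean A2 change = 1.820 / 17 = 0.107. Bias in the A1-to-A4 change = 0.5 × 0.107 = 0.05 SD.
- k = 4: 5.084 / 14 = 0.363. Bias = 0.5 × 0.363 = 0.18 SD. A simulation of the same mechanism gave 0.179.

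In this example dropout depends only on observed A1 and A2 values. A model that keeps those values is designed to handle it under missing at random. A completers analysis is not.

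**The case against.** Section 2.4 is an eligibility list and does not define an analysis set. The section that governs the analysis is explicit: intention to treat, all available data, complete cases not required. On that view the criteria are merely misplaced and Section 2.9 prevails. This stands in part. The article nowhere says that data from such patients are deleted, so a reader who infers that the trial will run a completers analysis goes further than the text. But no sentence says which section prevails, and the two give opposite answers for the same patient. This is a contradiction between two stated rules, not detail left to a fuller document.

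Several stronger readings are tempting and are not supported.

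- **That these events can occur only after randomisation.** A patient can miss A1, or withdraw between consent and the opening of the envelope. The criteria have a legitimate use before allocation; the fault is that they are not confined to it.
- **That the two analysis sets would be identical and the sensitivity analysis empty.** The per-protocol set also requires completion of the assigned intervention and further predefined criteria. The sets would largely overlap, no more.
- **That criterion (4) removes patients who take analgesics during follow-up.** Nothing applies it after allocation, and it stands among ordinary screening criteria. Its timing is ambiguous, and that is all that can be said.
- **That the bias is 0.35 SD.** This is the mean of the upper 80% of a normal distribution, 0.280 / 0.80 = 0.35. It requires one arm to lose exactly its worst 20% on the outcome itself (0.20 × 18 = 3.6, about 4 patients) while the comparator loses none. That does not match a loss of 11 of 54 across all arms. Where dropout depends on unobserved values, a missing-at-random model would not fully remove the bias either, so the figure cannot be charged to criteria (10) and (11).

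**Conclusion.** The point holds as a contradiction between Sections 2.4 and 2.9 over randomised patients who miss A2, A3 or A4 or who withdraw. If Section 2.4 were applied as written, the primary analysis would be close to a completers analysis.

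About 11 of 54 patients would be affected. This rests on the plan's 20% dropout and on all of that dropout falling under criteria (10) and (11). The direction and size of any bias cannot be known in advance. The range of 0.05 to 0.18 SD rests on the assumed one-arm mechanism, with equal variances and a correlation of 0.5, and is an illustration, not a forecast. If dropout were unrelated to response, there would be no bias from this source and only a modest loss of power on the interaction test.

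It should be corrected before analysis, because it concerns who is counted in the primary comparison.

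**What to change.** 1. In Section 2.4, remove (10) and (11) from the exclusion list, or limit them expressly to the time before the envelope is opened.
2. In Section 2.9, state that every randomised patient is analysed in the allocated group in the primary mixed model, with all visits available.
3. State that missed visits and withdrawal after allocation are recorded with their reasons and serve only to define the per-protocol set.
4. State the period to which criterion (4) applies for analysis purposes, and reconcile it with the intention-to-treat statement. This asks for consistency between the two sections; it does not propose any rule on analgesic use.

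The cost is a wording amendment to two sections, with no extra patients, visits or procedures.
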